#### Virus-negative comparison cohort

While the primary focus of the UNIVERSAL study is on hospitalised patients who test positive for a respiratory virus using the BioFire® FilmArray® System, a subset of virus-negative patients (n=100) is also being recruited (as per protocol amendment V.6.0, 20 September 2023). This group consists of individuals who present with respiratory symptoms but test negative for all viruses. This comparison cohort will allow for exploratory analyses of differences in clinical characteristics and outcomes between patients with confirmed viral infections and those in whom no virus is detected. All virus-negative participants provide written informed consent (see online supplemental material 1).

#### Selection of participants

The selection process involves a thorough review of medical records and clinical assessments to confirm eligibility based on the inclusion and exclusion criteria (figure 1). Trained research staff approach potential participants, providing detailed information about the study, including its objectives, procedures, risks and potential benefits. This ensures that participants can make an informed decision about their involvement in the study.

#### Consent procedure

All consent procedures adhere to ethical guidelines and relevant regulations, ensuring that participants’ rights and welfare are protected throughout the study. Participants with the capacity to consent are provided with detailed information about the study, including its purpose, procedures, risks and potential benefits. Written informed consent by completion of the informed consent form (online supplemental material 1) is obtained before any study-specific procedures are conducted.

The study complies with the Mental Capacity Act 2005. If a participant lacks the capacity to consent, a personal consultee such as a family member, carer, or friend may be approached to provide assent.

In cases where a personal consultee is not available, a nominated consultee may be sought. A nominated consultee is an independent person, usually a healthcare professional not connected to the research team, who can provide advice on whether the participant should join the study.

The personal/nominated consultee will be advised to set aside their own views and take into consideration the patient’s wishes and interests. Advance decisions and statements made by the patient about their preferences and wishes will always take precedence.

In the event of the patient recovering capacity following enrolment by the consultee, the patient will be asked to read the participant information sheet and provide consent for themselves. The patient may give consent, withdraw but have data and/or samples collected so far retained or withdraw and have their data and/or samples destroyed.

#### Participant withdrawal

The participant, or their consultee where a participant lacks capacity, is free to withdraw consent from the study at any time without providing a reason, and with no detriment to their medical care or legal rights. Investigators may withdraw a patient from the study in the interests of participant safety or the integrity of the research study.

### Data collection

Data will be collected at multiple time points: at admission, during hospitalisation and post-discharge. This comprehensive approach allows for detailed tracking of disease progression and recovery. The following sections outline the clinical data collected at each stage of the study (figure 2 and online supplemental material 2).

**Figure 2 F2:**
[figure not shown]
Data capture and timepoints for participants in the UNIVERSAL study. EQ-5D-5L, EuroQol 5-Dimension 5-Level; FACIT, Functional Assessment of Chronic Illness Therapy—Fatigue Scale; FLU-PRO PLUS, inFLUenza Patient-Reported Outcome Plus; GAD-7, Generalised Anxiety Disorder-7; HRG, Healthcare Resource Group; OSCI, Ordinal Scale for Clinical Improvement; PHQ-9, Patient Health Questionnaire-9; PRO, patient-reported outcome; RALE, Radiographic Assessment of Lung Edema; UNIVERSAL, Understanding Infection, Viral Exacerbation and Respiratory Symptoms at Admission-Longitudinal. Created with BioRender.com.

#### Baseline data collection (on admission)

On admission, detailed demographic information, medical history, clinical presentation and initial laboratory and imaging results are recorded. The initial treatment regimen is also documented.

#### In-hospital data collection

During hospitalisation, daily clinical assessments, including Ordinal Scale for Clinical Improvement (OSCI) score, oxygen requirements, symptom progression, repeated laboratory tests, follow-up imaging studies, treatment updates, complications and outcomes such as length of stay and discharge status, will be recorded.

#### Postdischarge data collection

Follow-up assessments are conducted at 1 week, 2 weeks, 4 weeks, 8 weeks, 12 weeks and 26 weeks postdischarge. These assessments monitor long-term recovery, including symptom resolution, new or persistent symptoms, quality of life, readmissions, long-term outcomes and ongoing medical needs and treatments. Data are gathered to analyse healthcare resource utilisation and time off from normal activities, specifically work and education.

#### Methods of follow-up

Follow-up methods include telephone calls and electronic surveys or postal methods, depending on the participant’s preference and logistical considerations. This thorough and structured follow-up schedule ensures detailed monitoring of participants’ recovery and long-term health outcomes, providing valuable insights into the natural history and economic impact of RVIs.

### Sample collection and Biobanking

All UNIVERSAL participants consent to provide biological samples as part of the study procedures. Samples are taken on day 1, 3 and 7 of enrolment while participants remain in hospital as detailed in online supplemental material 2. The biological samples provided include blood, upper respiratory tract swabs and nasal lining fluid. After initial storage at individual recruitment centres, samples are transferred to a secure UK biobanking facility for longer-term storage. Biological samples are anonymised and can be linked to clinical data collected as part of the study using anonymised participant identification numbers. In line with study objectives, this provides a biorepository of clinical samples to allow the exploration of inflammatory biomarkers associated with virus type and disease severity.

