### Participants

#### Eligibility criteria

Eligible participants for the UNIVERSAL study are identified on their admission to the hospital with respiratory symptoms. To qualify for the study, individuals must meet specific inclusion criteria at the time of screening. The eligibility criteria, recruitment process and participant pathway through the study are detailed in figure 1.

To be eligible, participants must be aged 18 years or older and exhibit features of an acute respiratory illness. This includes conditions such as acute upper or lower respiratory illnesses (eg, rhinitis, rhinosinusitis, pharyngitis, pneumonia, bronchitis and influenza-like illness) or an acute exacerbation of a chronic respiratory illness (such as chronic obstructive pulmonary disease (COPD), asthma or bronchiectasis). The diagnosis must be confirmed by a treating clinician. Additionally, participants must have been admitted as medical inpatients within the past 36 hours, with the admission time defined as the point at which the decision was made to admit the patient rather than the time of their arrival at the hospital.

Furthermore, participants must have a positive test result for RVI using the BioFire® FilmArray® System or other NHS Trust approved diagnostic PCR test during the current admission to be enrolled in the virus positive arm. A range of viral PCR platforms are employed by NHS Trusts in the UK which detect common respiratory viral pathogens including RSV, influenza and SARS-CoV-2. If on admission, a potential participant has tested negative using a limited respiratory virus PCR panel, once consented to UNIVERSAL, a respiratory tract swab sample is obtained and run on the BioFire® FilmArray® System to detect an extended panel of respiratory pathogens, including influenza A and B, RSV, SARS-CoV-2, parainfluenza viruses 1–4, human metapneumovirus, rhinovirus/enterovirus, adenovirus and coronaviruses 229E, NL63, OC43, HKU1. This ensures that a broad range of respiratory viral pathogens are included in the study. Participants who test negative for RVI have baseline data collected only. Participants are excluded from the study if they meet any of the following criteria: they or their consultee decline consent, they cannot undergo combined nasal and throat swabbing due to either personal refusal or a medical contraindication. Participants enrolled in the UNIVERSAL study who test positive for RVI, and complete study procedures cannot be enrolled a second time.

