### Variables

#### Primary outcomes

The primary outcomes of the UNIVERSAL study are focused on characterising the clinical impact of RVIs in hospitalised adults. This includes not only documenting the occurrence of various respiratory viruses, including influenza, RSV and SARS-CoV-2, but also a broader range of viruses such as rhinoviruses, parainfluenza viruses and human metapneumovirus. The study aims to evaluate their association with disease severity, progression and recovery. The study also aims to identify clinical and biological predictors of these outcomes, including markers such as viral load, inflammatory markers such as C reactive protein (CRP) and patient demographics. Another key outcome is measuring the duration of hospital stay for patients with RVIs and understanding the factors that contribute to prolonged hospitalisation.

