#### Demographic and clinical data

Demographic and clinical data are sourced from patient interviews and medical records. Detailed demographic information, including, sex, age at enrolment, height, weight, ethnicity, postcode, number of people in household and smoking history, is collected through structured patient interviews conducted by trained research staff. Medical history, including pre-existing comorbidities and vaccination history, is obtained from patient interviews and verified against medical records. Clinical presentation data, encompassing symptoms, duration of illness and severity scores such as the NEWS2 and OSCI, are documented using standardised assessment tools. Length of stay is addressed through review of clinical discharge summaries. During the discharge visit, details of treatments received during admission including time spent on intensive care or high dependency are collected from medical records. Mortality and readmission data are collected through medical records and patient interviews. While socioeconomic factors are not a primary focus of the study, participant postcodes are collected to allow for area-based deprivation analyses (eg, linkage to the Index of Multiple Deprivation).

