### Statistical methods

A detailed statistical analysis plan has been designed for the UNIVERSAL study involving all statistical considerations to ensure robust and reliable results. Here, we will only describe the essential statistical methods for the primary analysis. For analysis involving multiple comparisons, we will adjust them with Bonferroni correction. SAS V.9.4 or above, STATA V.18 or above and R V.4.4 or above will be used for analyses.

Descriptive statistics will be used to summarise baseline characteristics, clinical presentation and outcomes related to different viral pathogens. Measures of central tendency (mean, median) and dispersion (SD, IQR) will be calculated for continuous variables, while frequencies and percentages are used for categorical variables. Univariate analyses will be used to explore the relationship between key characteristics and the outcome measures. Clustering techniques will be used to explore similar patterns with respect to symptoms, severity and duration.

Multivariable regression models will be employed to identify associations between key predictors and outcomes while controlling for potential confounders. These models will be adjusted for demographic factors (age, sex, ethnicity, socioeconomic status, vaccination status), clinical variables (severity scores, comorbidities) and treatment regimens. Prior to model fitting, multicollinearity among covariates will be assessed using appropriate statistical methods (eg, variance inflation factor), and adjustments will be made if necessary to ensure model stability. The choice of regression model (eg, logistic regression for binary outcomes, linear regression for continuous outcomes) depends on the nature of the dependent variable. For analysis involving data at multiple time points, multilevel regression with first-level autoregressive error correlation structure (ie, AR(1)) will be used to control for within-subject correlation.

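### Viral load and biomarkers are not timed from symptom onset, and the named adjustment set leaves out the duration of illness that the study records, so virus contrasts and marker-outcome associations can partly reflect illness age

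*Protocol article*

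**What the plan says.** - **Sampling clock** (Sample collection and Biobanking): "Samples are taken on day 1, 3 and 7 of enrolment while participants remain in hospital". On what is taken: "The biological samples provided include blood, upper respiratory tract swabs and nasal lining fluid".
- **CRP** (Laboratory and imaging data): measured at baseline and again at discharge, a different schedule from the research samples.
- **Entry** (Eligibility criteria): "participants must have been admitted as medical inpatients within the past 36 hours", counted from the decision to admit. No limit on symptom duration is given.
- **Role of the markers**: Primary outcomes lists predictors of severity, progression and recovery, "including markers such as viral load, inflammatory markers such as C reactive protein (CRP) and patient demographics". Relating biomarkers to virus type is an exploratory objective, and biomarker profiles by clinical outcome also appear under Secondary outcomes.
- **What is recorded** (Demographic and clinical data): "Clinical presentation data, encompassing symptoms, duration of illness and severity scores such as the NEWS2 and OSCI, are documented using standardised assessment tools".
- **What is adjusted for** (Statistical methods): "These models will be adjusted for demographic factors (age, sex, ethnicity, socioeconomic status, vaccination status), clinical variables (severity scores, comorbidities) and treatment regimens". In the analysis text, duration appears only as one of the features to be clustered on.

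**The concern.** Day 1 is a study day, not an illness day. A first sample on illness day 2 and one on illness day 10 both count as day 1. Markers of acute infection are expected to move over the illness; the study's repeat sampling, and its definition of recovery partly by clinical markers returning to normal, presuppose this.

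Two kinds of estimate are exposed:

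1. **Virus contrasts.** If patients with one virus reach hospital later in the illness than patients with another, a difference in viral load or a biomarker may be a difference in sampling time.
2. **Marker-outcome associations.** If late presenters do worse and have passed their peak viral load, a low viral load would look harmful for reasons of timing.

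The models as listed could not tell these explanations from a real effect, although the variable needed to do so is on the case report form.

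**Working it through.** **1. The plan's own figures.** No stated figure is challenged. One bears on the fix: the prediction model needs 932 participants for an AUC of 0.85, 10% prevalence and up to 18 parameters. With the shrinkage criterion N = p / [(S − 1) ln(1 − R²/S)], S = 0.9 (assumed) and Cox-Snell R² = 0.1573 (derived from that AUC and prevalence), N = 18 / [(−0.1) × ln(1 − 0.1573/0.9)] = 937.1, so 938. This is within 1% of 932.

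**2. Bias in a virus contrast.** Let the marker be y = a − b·t + e, where t is days since onset, with no true virus effect. The unadjusted difference between two viruses is then b × D in size, where D is the difference in mean t. It is zero if b = 0 or D = 0. The documents give neither quantity, so all inputs below are assumptions.

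**3. Simulation.** Inputs: 150 per virus; onset times centred on 4 and 4 + D days with SD 3, cut off at zero; residual SD of the marker 1; 500 runs per row; two-sided 5% test. The cut-off makes the realised differences slightly smaller than b × D.

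| Onset difference D (days) | Fall per day (SD) | False difference, unadjusted (SD) | Rejection, unadjusted | False difference, adjusted for t (SD) | Rejection, adjusted |
|---|---|---|---|---|---|
| 0 | 0.1 | 0.00 | 4% | 0.00 | 4% |
| 0 | 0.2 | 0.00 | 5% | 0.01 | 6% |
| 1 | 0.1 | 0.09 | 11% | 0.00 | 5% |
| 1 | 0.2 | 0.18 | 28% | 0.01 | 6% |
| 2 | 0.1 | 0.19 | 35% | 0.00 | 6% |
| 2 | 0.2 | 0.38 | 84% | 0.00 | 7% |
| 3 | 0.1 | 0.29 | 68% | 0.00 | 4% |
| 3 | 0.2 | 0.58 | >99% | 0.01 | 6% |

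The Monte Carlo error of a 5% rate is √(0.05 × 0.95/500), about 1 percentage point, so the adjusted rates are close to nominal. On a viral-load scale, assumed falls of 0.1, 0.3 or 0.5 log10 per day and a 2-day gap give false differences of 0.2, 0.6 or 1.0 log10.

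**4. Bias in a marker-outcome association.** Suppose a continuous outcome rises by g per day since onset and does not depend on the marker. Regressing it on the marker alone gives a slope of −g·b·Var(t) / [b²·Var(t) + 1]. With Var(t) = 9 (ignoring the cut-off at zero), b = 0.1 gives −0.9g/1.09 = −0.83g, and b = 0.2 gives −1.8g/1.36 = −1.32g. The slope is zero if g = 0.

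**5. Parameter budget.** With R² and S fixed, N is proportional to the number of parameters. Taking 932/18 = 51.8 per parameter, 19 parameters need 984 and 20 need 1036. One parameter beyond 18 fits within the target of 1000; two do not.

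**The case against.** **The SAP may already cover this.** Statistical methods says that it gives only the essentials of the primary analysis and that a detailed plan exists. That is fair, and silence alone would be no finding. Here, however, the article names a specific set of covariates and leaves out a recorded one that fixes where in the illness each sample falls. If the SAP includes it, one line in the article settles the matter.

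**A reader might infer that the list is closed and shuts duration of illness out.** The text does not say so. Predictors names clinical presentation at admission as an open-ended group, and Demographic and clinical data counts duration of illness within clinical presentation. Duration is thus arguably in the predictor domain. That does not put it in the adjustment set for the biomarker models.

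**A reader might infer that CRP follows the day 1, 3 and 7 clock.** It does not; it follows baseline and discharge. It is equally unaligned to onset. Which sample yields viral load is not stated; the scheduled swabs are the natural reading.

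**A reader might infer that bias is certain.** It is not. It requires a difference in onset time between viruses, or a link between onset time and outcome, together with a marker that moves over time. The rejection rates come from simple two-group comparisons. The planned models carry other covariates, and multiple comparisons will be Bonferroni-corrected. Severity scores may absorb part of the effect, though they describe current state rather than illness age. Bonferroni correction lowers rejection rates but leaves the biased estimate unchanged.

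**Prediction differs from association.** A marker's value at presentation can be a valid predictor without adjustment for illness age. This stands, and it limits the fix. So does the point that starting the clock at enrolment is natural in a hospital cohort, where samples cannot precede consent; the remedy lies in the analysis, not the schedule.

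**Conclusion.** The point holds in conditional form. Biological measurements are not aligned to symptom onset, eligibility leaves symptom duration unrestricted, and the named adjustment set omits a recorded variable that would address this. Virus contrasts in viral load or biomarkers, and marker-outcome associations, can therefore partly reflect illness age.

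The size cannot be determined from the documents. It is about the daily marker change times the mean onset difference: 0.09 to 0.58 SD over the assumed 1- to 3-day gaps and 0.1 to 0.2 SD daily falls, and nothing if the gap is zero. The documents do not support saying that the bias will occur, or that every model is wrong without this term. Because the variable is already collected and the remedy is cheap, the change should be made.

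**What to change.** 1. **Association models** that use viral load, CRP or other biomarkers, as outcome or as predictor: add time from symptom onset to sample to the adjustment set. It equals the recorded duration of illness plus the lag to sampling.
2. **Virus contrasts**: report them with and without this term, so that readers can see how much depends on timing.
3. **The day 1, 3 and 7 series**: use days since onset as the time axis, or include it as a covariate alongside study day.
4. **Clinical prediction model**: offer duration of illness as a candidate predictor within the stated 18 parameters, rather than forcing it into every model.

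The cost is wording and one or a few extra parameters in the association models, with no new visits or samples. Self-reported onset carries some error, so adjustment may leave part of any bias in place; the results should say so.

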### Variables

#### Primary outcomes

The primary outcomes of the UNIVERSAL study are focused on characterising the clinical impact of RVIs in hospitalised adults. This includes not only documenting the occurrence of various respiratory viruses, including influenza, RSV and SARS-CoV-2, but also a broader range of viruses such as rhinoviruses, parainfluenza viruses and human metapneumovirus. The study aims to evaluate their association with disease severity, progression and recovery. The study also aims to identify clinical and biological predictors of these outcomes, including markers such as viral load, inflammatory markers such as C reactive protein (CRP) and patient demographics. Another key outcome is measuring the duration of hospital stay for patients with RVIs and understanding the factors that contribute to prolonged hospitalisation.

#### Secondary outcomes

Secondary outcomes provide a broader understanding of the long-term effects and economic impact of RVIs. These include evaluating the time required for patients to recover from their acute respiratory illness, defined by the resolution of symptoms and normalisation of clinical markers. The study also aims to analyse the direct and indirect costs associated with RVIs, covering hospitalisation costs, outpatient visits, medication expenses and loss of time from normal activities. Additionally, the study seeks to identify biomarker profiles associated with different clinical outcomes, which will aid in the development of precision medicine approaches.

#### Exposure—RVI

The primary exposure in the study is the presence of a confirmed RVI in hospitalised adults with acute upper or lower respiratory illnesses (eg, rhinitis, rhinosinusitis, pharyngitis, pneumonia, bronchitis and influenza-like illness), including acute exacerbations of chronic respiratory illnesses (such as COPD, asthma or bronchiectasis). This is determined using the BioFire® FilmArray® System or other validated clinical diagnostic PCR-based methods established at clinical sites during the patient’s current hospital admission.

The diagnostic criteria for RVIs in the UNIVERSAL study are based on laboratory confirmation using the BioFire® FilmArray® System or other PCR tests. Clinical diagnoses made by treating clinicians, supported by symptoms and imaging findings, are also used to categorise respiratory illnesses.

